## Abstract

**Background:**

There is broad consensus that diets high in salt are bad for health and that reducing salt intake is a cost-effective strategy for preventing chronic diseases. The World Health Organization has been supporting the development of salt reduction strategies in the Pacific Islands where salt intakes are thought to be high. However, there are no accurate measures of salt intake in these countries. The aims of this project are to establish baseline levels of salt intake in two Pacific Island countries, implement multi-pronged, cross-sectoral salt reduction programs in both, and determine the effects and cost-effectiveness of the intervention strategies.

**Methods/Design:**

Intervention effectiveness will be assessed from cross-sectional surveys before and after population-based salt reduction interventions in Fiji and Samoa. Baseline surveys began in July 2012 and follow-up surveys will be completed by July 2015 after a 2-year intervention period.

A three-stage stratified cluster random sampling strategy will be used for the population surveys, building on existing government surveys in each country. Data on salt intake, salt levels in foods and sources of dietary salt measured at baseline will be combined with an in-depth qualitative analysis of stakeholder views to develop and implement targeted interventions to reduce salt intake.

**Discussion:**

Salt reduction is a global priority and all Member States of the World Health Organization have agreed on a target to reduce salt intake by 30% by 2025, as part of the global action plan to reduce the burden of non-communicable diseases. The study described by this protocol will be the first to provide a robust assessment of salt intake and the impact of salt reduction interventions in the Pacific Islands. As such, it will inform the development of strategies for other Pacific Island countries and comparable low and middle-income settings around the world.

## Background

Non-communicable diseases (NCDs), including cardiovascular disease, cancer, diabetes and chronic respiratory disease are the leading cause of death in the world, killing more people each year than all other causes combined [1]. New Global Burden of Disease data indicate that one in four deaths worldwide were due to ischemic heart disease or stroke in 2010 [2] and that blood pressure is the most important global risk factor for health [3]. In response, the United Nations has established a target for all Member States to reduce NCD mortality by 25% by 2025 [4].

One of the main causes of high blood pressure is excess dietary salt intake. Excess salt intake progressively elevates blood pressure levels throughout life, which greatly increases the risks of vascular diseases [5,6] and is likely to be responsible for about half of the disease burden ascribed to high blood pressure [7]. Whilst there is still debate about the impact of salt reduction on cardiovascular disease, the totality of the evidence is convincing [8-10]. Much of the debate derives from the misinterpretation of weak research [11]. Carefully conducted overviews of the entirety of the evidence base consistently draw the same conclusions about the significant adverse effects of excess salt intake on health and the likely large health gains that can be achieved from population-wide salt reduction [12-14].

National and international organisations (including the Australian National Health and Medical Research Council [15], Health Canada [16], the American Heart Association [11], and the World Health Organization [13,17]) advocate for programs that will reduce salt intake. In addition, Member States at the World Health Assembly in Geneva in May 2013 agreed on a global target to reduce salt by 30% by 2025 [4].

The physiological requirement for salt is less than 1 gram per day [18] but, in populations where salt has been measured, average daily intakes are between 9 and 12 grams [19]. Interventions to reduce salt have demonstrated effectiveness in developed (high income) countries. Japan and Finland both implemented successful salt reduction strategies in the 1970s [20,21] and the UK’s salt reduction program, launched in 2003, has reduced average daily salt intake by about 1.5 grams (from 9.6 to 8.1 grams) in the last decade [22].

A recent review of salt reduction strategies in 32 countries [23] identified baseline data about salt intake levels and patterns as a clear prerequisite for the successful design and implementation of effective interventions. Most programs included work with the food industry to reduce the salt content of foods and meals, in parallel with campaigns to change consumer behaviour [23-25]. Voluntary or mandatory initiatives to address labelling and work to change the food environment through settings, such as schools and hospitals, were also key elements of many strategies.

Whilst there is a growing body of evidence about the likely effectiveness of different strategies to reduce salt intake, there are fewer data about their likely cost-effectiveness; and a paucity of data on salt from low and middle-income countries [26]. In Pacific Island countries, an increased reliance on processed foods is contributing to the rise in the incidence and prevalence of NCDs [27-29]. Approximately 40% of all 9.7 million Pacific Island citizens have been diagnosed with a NCD, mainly cardiovascular disease or diabetes, and/or have hypertension [30].

Surveys in a number of Pacific Islands countries, using the WHO STEP-wise approach to chronic disease risk factor surveillance (STEPS) [31], have confirmed high blood pressure to be a significant NCD risk factor [32,33]. Salt intake is almost certainly a key contributor to this problem with high sodium foods, such as bread, margarine, crackers, noodles, canned foods, butter, soy and other sauces, now staples for many households [28]. However, salt intake patterns have not been systematically and objectively evaluated to date. While the limited available information suggests high salt levels in many Pacific Island countries, more detailed country specific information is required to mount, and garner multi-sector support for, salt reduction programs [34]. For most countries it appears that a population-wide salt reduction program would potentially be one of the most cost-effective ways of improving population health [35], but the evidence to drive concerted action is mostly absent [26].

This project, funded through the Global Alliance for Chronic Disease (GACD) Hypertension Program, will help to fill these gaps in the evidence. The Program is the first initiative of its kind with the world’s largest funders of medical and health research coming together to fund research into non-communicable diseases (NCDs). Each of the fifteen research projects are being conducted through partnerships between investigators from institutions in high-income and low-and middle-income countries. A key focus of the program is implementation science and translation of evidence into policy and practice.

## Methods/Design

The study will employ a before-after design. Baseline (2012) and follow-up surveys (2015) will be conducted either side of a multi-pronged, cross-sectoral intervention that seeks to reduce population salt intake in Fiji and Samoa over two years. The study will be conducted in three phases and will use both quantitative and qualitative research methods. Broadly, these three phases constitute:

*– Phase I- Baseline assessments* comprising population surveys of salt intake, surveys of the salt content of foods in shops, participatory community research to understand stakeholder views, and an audit of current practice.

*– Phase II – Intervention development and implementation* using the baseline information to formulate a comprehensive policy response and action plan to reduce population salt intake.

*– Phase III – Evaluation of impact* through follow-up community surveys, surveys of foods in shops and a cost-effectiveness analysis.

### Study objectives

The overall study objective is to assess the effect of a multi-pronged, cross-sectoral intervention program to reduce population salt intake in both Fiji and Samoa. Secondary objectives include determining the effects of the salt reduction program on population knowledge, attitudes and behaviour by comparing mean population levels at baseline and follow-up and determining the effects of the salt reduction program on average levels of sodium in foods based upon food composition surveys that collect data from food labels at baseline and follow-up. The project will also consider the effects of the salt reduction intervention on dietary salt by examining changes in diet based on the Food Frequency Questionnaires (FFQs) administered at baseline and follow-up in each country. The relationship between salt intake measured by 24-hour urine and salt intake estimated from spot urine will also be explored.

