### Outcomes

#### Primary

The primary outcome of the study will be the change in 24-hour urinary salt level in the overall study population (in each country). If a positive impact is demonstrated, then a cost-effectiveness assessment will also be undertaken.

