#### Secondary outcomes

The main secondary outcomes will be changes in knowledge levels and current practices relating to salt and changes in the mean concentration of sodium in foods.

Additional outcomes will include changes in the composition of diet based on the FFQs and understanding of the relationship between salt intake measured by spot and 24-hour urine in each country. The latter is important as, if it proves possible to use spot urines to estimate 24-hour urinary sodium excretion, in future this would provide a more feasible and practical alternative to measuring salt intake for countries.

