#### Sampling strategy

The study population will be adults aged 18–69 years in both countries. Baseline salt assessment and questions on knowledge, attitudes and behaviours related to salt (KAB) will be integrated into the WHO STEPS survey in Samoa and the STEPS sampling framework will be used in Fiji. The framework uses a stratified (province or division) three-stage (enumeration area, household and individual) cluster random sampling process using probability proportional to size to obtain representative samples for the STEPS survey in each country based on the statistical regions identified in recent Censuses [36-38]. Sub-samples (e.g. every fifth person, so as to recruit 250 men and 250 women) will then be selected to collect 24-hour and spot urines.

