#### Data collection and management

Interviewer administered questionnaires will be used to obtain demographic and risk factor related information, including knowledge, awareness and practices related to salt from all participants. In addition, dietary intake will be assessed by trained research assistants using food frequency questionnaires (FFQs) on the sub-sample. The FFQ has been previously used to measure population salt intake in Fiji [39]. It will be adapted for Samoa, informed by the list of foods collected during the STEPS survey. Spot and 24-hour urine samples will be collected for each participant in both countries in accordance with established protocols [40]. All methods will be piloted as part of the training processes in each country.

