#### Salt reduction intervention

While the nature of the salt reduction intervention strategies will be informed by the outcome of the stakeholder consultation and other baseline data collected during the project, it is likely that the program will include core components and approaches employed elsewhere. In addition, the strategies will reinforce existing national programs being implemented by the Ministry of Health and key agencies in each country. Core components of the programs will include: (i) the food industry (including caterers, bakers, importers, processors and retailers) with efforts directed towards reducing average salt levels in locally manufactured and imported foods towards agreed targets for salt levels in foods, work to facilitate the catering and food service sectors to provide low salt meals and initiatives related to labelling of foods in stores and food service outlets; (ii) consumers through targeted and sustained campaigns to change awareness and behaviours related to salt with a focus on children and using culturally appropriate communication channels including church leaders and women’s groups; and (iii) settings such as schools, hospitals and the workplace through the establishment of standards and educational campaigns.

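### The before-after FFQ change is the stated route to the intervention's effect on dietary salt, although the salt campaign may shift reporting; check it against 24-hour urine from the same people

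*Protocol article*

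**What the plan says.** All references are to the protocol article.

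- **Study objectives** plans to assess "effects of the salt reduction intervention on dietary salt by examining changes in diet based on the Food Frequency Questionnaires (FFQs) administered at baseline and" again after the intervention. The FFQ comparison is thus worded as a way to see an intervention effect on salt.
- **Secondary outcomes** ranks it below the main secondary outcomes: "Additional outcomes will include changes in the composition of diet based on the FFQs".
- **Data collection and management** (population surveys): "dietary intake will be assessed by trained research assistants using food frequency questionnaires (FFQs) on the sub-sample". The section on recruitment has trained health research staff collecting data face to face.
- **Sampling strategy**: "Sub-samples (e.g. every fifth person, so as to recruit 250 men and 250 women) will then be selected to collect 24-hour and spot urines". FFQ and 24-hour urine are therefore both planned for the same sub-sample.
- **Salt reduction intervention** includes "targeted and sustained campaigns to change awareness and behaviours related to salt" among consumers.
- **Discussion** acknowledges that there is no control group.
- The one comparison of measurement methods that is announced concerns the two urine measures: "The relationship between salt intake measured by 24-hour urine and salt intake estimated from spot urine will also be explored". No section announces a comparison of FFQ salt with 24-hour urine.
- **Primary** defines the primary outcome as the change in 24-hour urinary salt in each country.

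**The concern.** A constant error in a questionnaire largely cancels when two rounds are compared. An error that changes because of the intervention does not. Here the intervention tells the surveyed population that salt is harmful, and health research staff then ask that population what it eats. Respondents at follow-up have more reason than respondents at baseline to understate salty foods, and the plausible direction of that shift is towards benefit.

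If this happened, FFQ salt could fall with no change in intake. Under the wording of the objective, that fall could be read as an effect of the programme on dietary salt, either as the dietary explanation of a urinary change or as a favourable result when urine does not move. An objective marker is already collected in the same people, yet the article does not say it will be set against the FFQ.

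**Working it through.** **1. The plan's own figure.** Inputs from the sample size section: mean 160 mmol/day, SD 48 mmol, 500 per survey per country, alpha 0.05 (two-sided assumed), 80% power, 8.5 mmol (about 0.5 g salt), 1 g salt = 17.1 mmol. With independent surveys and simple random sampling:

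(1.960 + 0.842) × 48 × √(2/500) = 8.51 mmol; power at 8.5 mmol = 79.95%.

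The stated 80% reproduces. It serves below only as a yardstick.

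**2. How large a reporting shift would matter.** The documents give neither an FFQ mean or SD nor a size for any reporting shift. Assume that mean FFQ sodium is also 160 mmol (160/17.1 = 9.36 g salt), that its SD is also 48, and that true intake does not change. The last column is the power of the two-sample comparison of FFQ means, n = 500 per round.

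| Assumed fall in reporting | Apparent fall, mmol (160 × %) | Apparent fall, g salt (÷ 17.1) | Chance of a significant false difference |
|---|---|---|---|
| 2% | 3.2 | 0.19 | 18% |
| 3% | 4.8 | 0.28 | 35% |
| 5% | 8.0 | 0.47 | 75% |
| 8% | 12.8 | 0.75 | 99% |
| 10% | 16.0 | 0.94 | over 99.9% |

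A shift of 8.5/160 = 5.3% would equal the whole target difference. The base is a urinary planning value applied to a questionnaire, so this shows scale and does not predict a bias.

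**3. What the data in hand can show.** The rounds are separate cross-sections. The pairing available is therefore FFQ with urine within a person at each round, and the quantity of interest is the between-round change in the mean of (FFQ sodium − urinary sodium). With 500 complete pairs per round and simple random sampling:

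| Assumed SD of the within-person difference | Change detectable with 80% power | Power for an 8 mmol (5%) shift |
|---|---|---|
| 48 | 8.5 mmol | 75% |
| 60 | 10.6 mmol | 56% |
| 72 | 12.8 mmol | 42% |

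For example, at SD 60: 8 / (60 × √(2/500)) = 2.11, and Φ(2.11 − 1.96) = 0.56. The check is informative but cannot exclude a shift of the size in step 2. Clustering and incomplete pairs would lower its power further.

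**4. Whether the check can also correct the FFQ.** Let F be the FFQ mean and U the urinary mean in a round, with ratio R = F/U. Rescaling gives F/R = U, so the rescaled FFQ change is simply the urinary change, which is the primary outcome. A single multiplier also cannot repair under-reporting that is selective by food. The comparison is a diagnostic and not a correction.

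**The case against.** The strongest reply has four parts.

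- *The article is condensed.* It has no analysis section for the FFQ, and a check for misreporting could sit in a full protocol or analysis plan that is not shown. This stands as far as the missing comparison goes. It does not dispose of the wording in the objectives, which ties FFQ change to an intervention effect in the text itself.
- *The outcome ranks low.* The FFQ is an additional outcome, worded as composition of diet, and the effect on salt intake is judged on 24-hour urine. This stands and limits the weight of the point. A reader might infer that the main conclusion is at risk, or that the urine data go unused; neither follows. Urine is the primary outcome, and all that is absent is its use as a check on the FFQ. Nor does any section say that FFQ change would stand in for a null urinary result.
- *The bias is not demonstrated.* A reader might infer that the campaign does change reporting. The documents support only that it may. The 5% is an assumption, on a base that is not an FFQ mean.
- *Agreement can move for other reasons.* Reformulation, or a change in salt that the FFQ does not capture, would shift it too. The food surveys cover the foods contributing most salt, in the largest stores of the main urban centres, so they do not supply round-specific composition for every FFQ item. In Samoa, urine collection is integrated into the STEPS survey while the FFQ is adapted from foods listed during that survey, so the two may not coincide in time at baseline. All of this stands and argues for reading the comparison as a diagnostic.

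**Conclusion.** The point holds in a limited form. The objective reads the before-after FFQ change as showing effects on dietary salt, while a sustained awareness campaign, self-report to health staff and the absence of a control group leave changed reporting and changed diet inseparable within the FFQ data. The primary outcome is not open to this bias.

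The size is unknown. If the FFQ mean is near 160 mmol, a reporting shift of about 5% would imitate the 0.5 g target; the range for 2% to 10% is 0.19 to 0.94 g. These rest on an assumed shift and on a mean and SD borrowed from the urinary planning values.

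The documents do not support stronger conclusions: that reporting will change, that the primary result is compromised, or that the FFQ can be rescued by rescaling it to urine. A rule that accepts FFQ change only when agreement is stable would not be sound either. It has no natural threshold, and power of 42% to 75% for an 8 mmol shift (at the assumed SDs) would let a non-significant result pass as stability. This is a cheap improvement to an additional outcome.

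**What to change.** Amend Study objectives and Secondary outcomes to state that:

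1. For sub-sample members with both measures, the mean difference (or ratio) between FFQ-estimated sodium and 24-hour urinary sodium will be reported at each round, with its between-round change and 95% CI, separately for Fiji and Samoa.
2. FFQ results will be described as change in reported diet and read beside the urinary change.
3. FFQ change alone will not be cited as evidence that salt intake fell.
4. The interval in time between FFQ and urine collection will be reported for each round and country, in particular for Samoa at baseline.

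Do not add a rescaling step or a pass/fail rule on agreement; report the estimate with its interval and let the reader weigh it.

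The cost is a few sentences and one analysis of measures already planned. The downsides are that the FFQ outcome may look less favourable, and that a change in agreement will not by itself say whether reporting, reformulation or uncaptured salt is the cause. Composition data should be specific to the round wherever the food surveys allow, and the remaining gaps stated.

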### Outcomes

#### Primary

The primary outcome of the study will be the change in 24-hour urinary salt level in the overall study population (in each country). If a positive impact is demonstrated, then a cost-effectiveness assessment will also be undertaken.

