### Cost-effectiveness analysis

Incremental cost-effectiveness analysis will be undertaken to determine whether the intervention strategy in each country represents ‘value-for-money’ measured against current practice. It will address issues of both technical efficiency (‘how to do it’) through assessment of key design features of the intervention strategy and the associated cost drivers, and allocative efficiency (‘what to do’) through the modelling of longer term consequences and cost offsets. The analyses will be conducted from a societal perspective for the 2013 reference year. Pathway analysis (‘who does what to whom, when and where and how often’) will be used to specify resources associated with the interventions. Detailed documentation of all activities undertaken, and their associated resource costs, will be conducted throughout the study duration to facilitate comprehensive costing of interventions (excluding and including measurements).

Economic modelling will be used to extend the target population, time horizon and decision context for the cost-effectiveness analysis. The incremental change in salt consumption, as a result of the intervention strategy, will be converted to savings in Disability-Adjusted Life Years (DALY) over the lifetime of the national cohort (Fiji and Samoa separately), with the resulting incremental cost-effectiveness ratios expressed as cost per DALY saved. Standard discounting will be applied to both costs and outcomes. Simulation-modelling using the @RISK software package will be employed to calculate 95% uncertainty intervals (around the median) about the efficacy and cost estimates.

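### The cost-effectiveness analysis depends on an undefined positive result in one section but is promised without condition in three others

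*Protocol article*

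**What the plan says.** Four places in the protocol article bear on whether the economic analysis is done.

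- **Outcomes – Primary**, directly after defining the primary outcome as the change in 24-hour urinary salt in each country: "If a positive impact is demonstrated, then a cost-effectiveness assessment will also be undertaken". The article does not say whether this turns on significance, direction or size, or whether each country is judged separately.
- **Abstract, Background**: one project aim is to "determine the effects and cost-effectiveness of the intervention strategies".
- **Methods/Design**: Phase III evaluates impact through "follow-up community surveys, surveys of foods in shops and a cost-effectiveness analysis".
- **Cost-effectiveness analysis**: "Incremental cost-effectiveness analysis will be undertaken to determine whether the intervention strategy in each country represents" value for money against current practice.

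The last three carry no condition. The Cost-effectiveness analysis section also fixes the effect input, with a lifetime horizon for each country's cohort: "The incremental change in salt consumption, as a result of the intervention strategy, will be converted to savings in Disability-Adjusted Life Years (DALY". It plans simulation that "will be employed to calculate 95% uncertainty intervals (around the median) about the efficacy and cost estimates", and says that activities and their resource costs are documented throughout the study.

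**The concern.** After a null or mixed result, the same document could be cited for running the economic analysis or for dropping it, and the choice would be made with the result in view.

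If the condition is followed, two things happen. First, a country with a real but inconclusive reduction gets no economic answer. A modest reduction can still be good value, and the Background names the shortage of cost-effectiveness data as a gap that the project will help to fill. Second, economic results come into being only when the salt estimate has passed a hurdle. Estimates selected in this way are too large on average, and the article states no allowance for the selection. The Abstract's Discussion expects the study to inform strategies in other countries, so it matters which results exist.

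**Working it through.** **Inputs.** From Sample size: SD 48 mmol, 500 participants per survey per country, alpha 0.05, detectable difference 8.5 mmol, stated power 80%, and 1 g salt = 17.1 mmol sodium. Two inputs are my assumptions:

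- A demonstrated positive impact means a reduction significant at two-sided 0.05.
- Where a design effect (DEFF) is used, it is 1.5. The article specifies three-stage cluster sampling but gives no value.

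**Step 1: reproduce the plan's figure.** With independent surveys and no design effect, SE = 48 × √(2/500) = 3.036 mmol. The significance threshold is c = 1.96 × 3.036 = 5.95 mmol. Power at 8.5 mmol = Φ((8.5 − 5.95)/3.036) = Φ(0.840) = 0.7995. The stated 80% reproduces as a two-sided test without a design effect; a one-sided 0.05 test would give 87.6%.

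**Step 2: how often the analysis would be missing.** This is 1 minus the probability of passing the threshold.

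- No design effect, true 8.5 mmol: 1 − 0.7995 = 0.20.
- DEFF 1.5: SE = 48 × √(2 × 1.5/500) = 3.718 and c = 7.287. The probability of passing is Φ((8.5 − 7.287)/3.718) = 0.628, so the analysis is missing with probability 0.37.

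**Step 3: mean estimate among studies that pass.** For a true change d, let a = (c − d)/SE. Then E[estimate | passes] = d + SE × φ(a)/(1 − Φ(a)).

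- No design effect, d = 8.5: 8.5 + 3.036 × 0.2803/0.7995 = 9.56 mmol, a ratio of 1.125. Simulation gave the same ratio.
- DEFF 1.5, d = 8.5: 10.74 mmol, a ratio of 1.264.

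| True change (mmol) | Passes, DEFF 1 | Ratio, DEFF 1 | Passes, DEFF 1.5 | Ratio, DEFF 1.5 |
|---|---|---|---|---|
| 4.25 | 0.288 | 1.85 | 0.207 | 2.21 |
| 6 | 0.507 | 1.40 | 0.365 | 1.64 |
| 8.5 | 0.800 | 1.125 | 0.628 | 1.26 |
| 12 | 0.977 | 1.01 | 0.898 | 1.06 |
| 17.1 (1 g salt) | 1.000 | 1.00 | 0.996 | 1.00 |

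**Step 4: the weaker reading of the condition.** If any favourable point estimate is enough, set c = 0.

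- At 8.5 mmol the analysis runs with probability 0.997 and the ratio is 1.003 (0.989 and 1.013 at DEFF 1.5).
- At 4.25 mmol the figures are 0.919 and 1.12 (0.873 and 1.21 at DEFF 1.5).

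**Step 5: without the condition.** Every estimate enters the model, so the mean input equals the true change and no country is left without an analysis.

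**The case against.** The texts can be partly reconciled. One section says whether the analysis is run and another says how, the phase list is offered only as a broad outline, and a specific condition may qualify a general summary. Cost-effectiveness does not appear under Study objectives or Secondary outcomes. That makes the conflict milder but does not remove it: the Abstract states cost-effectiveness as an aim, and the dedicated section says that the analysis will be done in each country.

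Requiring evidence of effect before lifetime modelling is also a defensible use of resources, and a cost per DALY is unstable or undefined near zero effect. This stands as a reason to choose the form of presentation carefully. It does not justify leaving the condition undefined.

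The strongest objection concerns bias. A reader might infer that the condition pushes an exaggerated effect into this study's cost per DALY, by 1.6 to 1.9 times. The documents do not support that, for two reasons.

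- If the result is positive, the salt change entering the model is the same with or without the condition. The exaggeration is an average over repeated studies, and deleting the condition changes only whether a country without a positive result is modelled too.
- The large figures come from borrowing the UK programme, which "has reduced average daily salt intake by about 1.5 grams (from 9.6 to 8.1 grams) in the last decade". Prorated to two years this is 0.3 g × 17.1 = 5.13 mmol. Under the significance reading, the mean passing estimate is then 8.10 mmol (1.58 times the truth), or 9.59 mmol (1.87 times) at DEFF 1.5. The plan does not adopt that effect; it is powered for 8.5 mmol. Prorating the article's 30% target for 2013 to 2025 in the same way gives 160 × 0.30 × 2/12 = 8 mmol, close to the planned value.

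It is also fair that the planned simulation already covers uncertainty in the efficacy estimate, so part of the remedy is in place.

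**Conclusion.** The contradiction holds: one section imposes an undefined condition that three others do not carry. Its main consequence is a lost answer to a stated aim. Under the significance reading, this happens about 20% of the time at a true 8.5 mmol with no design effect, and about 37% at the assumed design effect of 1.5.

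The secondary consequence is selection. The economic results that exist would rest on salt changes averaging 1.125 times an 8.5 mmol truth (1.26 times at DEFF 1.5). The excess rises for smaller true effects and nearly vanishes from about 12 mmol with no design effect. Both consequences are negligible at 8.5 mmol if a favourable point estimate is enough, though not at half that change. The primary estimate itself is unaffected.

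Severity is minor to moderate. The sizes depend on the reading of the condition, the true effect and the design effect, and the article fixes none of these for this purpose.

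**What to change.** Delete the conditional sentence under Outcomes – Primary, or replace it with a statement that the cost-effectiveness analysis will be done in each country whatever the primary result. The section then agrees with the Abstract, Phase III and the Cost-effectiveness analysis section.

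In the planned simulation, draw the salt change from its full sampling distribution under the survey design, including values at or below zero. Present the result in a form that stays defined near zero effect, for example incremental costs and incremental DALYs, or the probability of cost-effectiveness, alongside any ratio.

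If the sponsor prefers to keep a condition, it should define a positive impact (criterion, direction, and country by country or jointly), repeat the condition in the other three places, and state that the economic results are conditional on it.

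The cost is one sentence, plus the modelling work in a country with a null result. Cost data are already to be collected throughout and the simulation is already planned, so no new data collection is needed.
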